##### Secondary outcomes

2.15.1.2

The secondary analyses will evaluate the between-group difference in secondary outcomes (Table 1) over 12 months using the same LMM structure as the primary analysis. In addition, the raw wrist monitor accelerometer and PPG data collected at baseline and at 12 months (each for a one-week period) will be processed to derive information on physical activity and sleep. We will use algorithms developed in-house at the Radboudumc (76) and in collaboration with Eindhoven University of Technology (TU/e) (77) to process the raw data into interpretable metrics such as total physical activity, sedentary behavior, sleep duration and sleep quality. After processing the data, average values across the one-week periods will be calculated per participant at each timepoint. The within-subject changes from baseline to 12 months will be compared between groups using a LMM with the same structure as the primary and other secondary analyses.

##### Cost-effectiveness analysis

2.15.1.3

The cost-effectiveness analysis will be conducted from both a healthcare and societal perspective. This analysis will include direct healthcare costs, such as, resource use during the intervention and standard care, as well as broader societal costs, including caregiver burden and productivity losses. Quality-adjusted life years (QALYs) will be calculated based on responses to the EQ-5D-5L. The primary outcome of the analysis will be the Incremental Cost-Effectiveness Ratio (ICER). To account for uncertainty in model parameters, a Probabilistic Sensitivity Analysis (PSA) will be performed using Monte Carlo simulation. The results of the PSA will be visualized using a Cost-Effectiveness Plane, and a Cost-Effectiveness Acceptability Curve (CEAC), illustrating the probability of cost-effectiveness across a range of willingness-to-pay (WTP) thresholds. In addition, a Deterministic Sensitivity Analysis (DSA) will be conducted to assess robustness of the results to variations in key parameters. The results of the DSA will be presented using a tornado diagram. Several additional scenario analyses may also be performed to explore alternative assumptions and perspectives.

#### Methods for additional analyses

2.15.2

Exploratory mediation analyses will be performed on the primary outcome (PDQ-39 total score) to assess the potential mediating role of psychosocial constructs, including general self-efficacy (GSES), coping style (WCQ), and self-management (PAM). Exploratory subgroup analyses will be conducted to investigate effects based on the specific lifestyle domain participants focused on during the intervention. Specifically, we will explore (1) whether there are differences in QoL between participants who targeted different lifestyle domains, (2) multiple lifestyle domains versus a single domain, and (3) whether participants show improvements in outcomes directly related to the domain they worked on. For example, whether those who focused on the sleep domain demonstrate an improvement in insomnia and sleep quality. We hypothesize that participants may show greater improvements in outcomes directly related to the lifestyle domain they actively targeted. Furthermore, we will perform exploratory subgroup analyses based on disease duration. Participants will be categorized into three groups: <5 years, 5–10 years, and >10 years since disease onset.

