### Trial design

2.1

The SENSS study is a 12-month single-blind, randomized controlled trial (RCT). The intervention group receives a combined lifestyle intervention (SENSS approach) after a personalized intake and with continuous monitoring by a lifestyle coach. The control group only receives the personalized intake with a lifestyle coach, but continues with usual care. A total of 256 individuals with PD will be included, equally randomized into the control and intervention group. Participants complete three remote assessments: at baseline, 6 months, and 12 months follow-up. An overview of the study design is provided in Figure 2.

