### Intervention

2.5

The intervention is a personalized and stepped care lifestyle intervention (SENSS) that combines five different and complementary lifestyle domains (stress, exercise, nutrition, sleep and self-management). In this intervention, self-management complements four important lifestyle domains, as it plays an overarching role in lifestyle behavior.

In the SENSS approach, participants receive guidance by a trained lifestyle coach. The title of lifestyle coach is not legally protected in the Netherlands. To ensure intervention quality, lifestyle coaches delivering the intervention are required to be affiliated with the Dutch professional association for lifestyle coaches (Beroepsvereniging Leefstijlcoaches Nederland; BLCN). BLCN affiliation requires compliance to strict admission standards and ongoing professional development. This includes holding at least a bachelor’s degree at a university of applied sciences level and having completed a BLCN-accredited postgraduate lifestyle coaching program, or having successfully completed an individual accreditation pathway (33). For this trial, two certified and dedicated lifestyle coaches will provide the intervention. Participants are divided pragmatically between the two lifestyle coaches, based on coach availability at the time of enrolment.

The SENSS approach starts with goal setting using a lifestyle decision aid, previously developed by our group in accordance with the International Patient Decision Aid Standards (22, 34). The Parkinson lifestyle decision aid (35) is a web-based tool. The tool includes information and questions that support people with PD to identify their needs in relation to lifestyle, set goals, make a plan, and determine the type of support they may need. The questions range from mapping the current situation in relation to their lifestyle, to clarifying their values, preferences and goals for all five lifestyle domains and identifying the needs for support to reach sustainable changes in lifestyle. The decision aid concludes with a summary of the answers given. This summary serves as a starting point for the consultation with the lifestyle coach, during which shared decision making is used to determine which lifestyle domain(s) to prioritize and what level of support is appropriate. For the participants in the intervention group, this level of support is further specified in a stepped care model (Figure 3).

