**Figure 3 fig3:**
[figure not shown]
The stepped care model.

The stepped care model is used to provide just the right amount of guidance. By following the steps in the model, people with PD are encouraged to work on their lifestyle goals independently, supported by technological tools when possible (self-management). Professional support is provided when needed, based on participant reported needs and the lifestyle coach’s professional judgment. The approach is highly personalized, meaning participants do not have to follow a fixed sequence of steps. They can move between steps in either direction throughout the intervention. Importantly, a lifestyle coach will continuously monitor adherence and progress, and discusses with the participant whether changes are needed in either the lifestyle domain they are working on or in the level of support. The frequency of monitoring is decided through shared decision making by the lifestyle coach and participant, within a range of once every month to once every 3 months. In the following paragraphs the different steps will be described in more detail.

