### Participant timeline

2.7

Initially, an assessor from the research team sends an information letter and informed consent to potential participants. Two weeks later, a phone call is planned with the participants, during which they have the opportunity to ask questions. If they are still willing to participate, participants undergo a brief cognitive assessment over the phone to determine eligibility and informed consent will be obtained. Upon signing the informed consent, participants will receive multiple questionnaires for the baseline assessment which they can complete at home, at their own pace within two weeks. Reminder emails will be sent after two and four weeks, followed by telephone contact after six weeks if questionnaires remain incomplete. After the baseline questionnaires have been returned, participants will be randomly allocated into the control or intervention group. Within two weeks after completing the questionnaires participants will receive a package. Some participants will receive a package containing a wrist monitor. The monitor will be worn one week at the start of the study and one week at the end. The package also includes a “part 2.” After the week in which the participant has worn the monitor, part 2 of the package can be opened. It contains the randomization result and login details for the lifestyle decision aid. Participants can contact a helpdesk during office hours for additional information or guidance on how to use the wrist monitor or decision aid if needed. Participants who receive a package without wrist monitor can open the randomization results and login details for the lifestyle decision aid immediately.

The lifestyle coach will schedule an intake meeting with participants two weeks after the package delivery. The participants are required to complete the lifestyle decision aid before the meeting. Participants in the intervention group schedule a follow-up meeting with the lifestyle coach during the intake, typically one to three months later, based on personal goals and needs. The control group receives no further coaching after the intake.

All participants will receive a set of questionnaires at T1 and T2. Importantly, participants will not be required to visit the research location at Radboudumc. All research procedures can be performed from their own home.

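### The exploratory lifestyle-domain analyses group participants by a domain chosen after randomisation, so regression to the mean can look like domain-specific benefit; pre-randomisation T0 scores would allow a randomised contrast

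*Protocol article*

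**What the plan says.** All references are to the protocol article.

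- **Grouping (2.15.2, Methods for additional analyses).** "Exploratory subgroup analyses will be conducted to investigate effects based on the specific lifestyle domain participants focused on during the intervention".
- **Questions 1 and 2 (same section).** The comparisons are "whether there are differences in QoL between participants who targeted different lifestyle domains, (2) multiple lifestyle domains versus a single domain".
- **Question 3 (same section).** This asks about improvement in the outcome belonging to the chosen domain. The example given is "whether those who focused on the sleep domain demonstrate an improvement in insomnia and sleep quality".
- **Direction expected (same section).** "We hypothesize that participants may show greater improvements in outcomes directly related to the lifestyle domain they actively targeted".
- **How the domain is chosen (2.5, Intervention).** The decision-aid summary feeds a consultation with the coach, "during which shared decision making is used to determine which lifestyle domain(s) to prioritize and what level of support is appropriate".
- **The choice is not fixed (2.5, text under Figure 3).** As part of ongoing monitoring, the coach "discusses with the participant whether changes are needed in either the lifestyle domain they are working on or in the level of support".
- **Control arm (2.1, Trial design).** "The control group only receives the personalized intake with a lifestyle coach, but continues with usual care". The decision aid applies to both arms: "The participants are required to complete the lifestyle decision aid before the meeting" (2.7, Participant timeline).
- **Order of events (2.7).** Baseline questionnaires are returned first, then randomisation takes place. The decision-aid login reaches the participant together with the allocation result.

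**The concern.** Randomisation protects a comparison between arms. It does not protect a comparison between people who chose different things after they were allocated. The domain groups are formed at the intake, after allocation is known, and can be revised in the light of progress. Membership can therefore reflect need, motivation and continued participation as well as the intervention.

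The third question is the most exposed. People who choose sleep are likely to include many whose sleep was poor at baseline, and a group selected partly for a poor score tends to score better on remeasurement without any treatment effect. Section 2.15.2 names no control comparator for this question, and the artefact runs in the direction of the stated hypothesis. A report that targeted outcomes improved more could follow from the way the groups were formed.

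The first two questions compare quality of life between groups that differ in need and engagement. The multiple-versus-single question matters because the Introduction (1.1) rests part of its case on a possible added benefit of combining domains.

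**Working it through.** **1. The plan's own figure.** Section 2.8 gives a difference of 4.15, an SD of 10.55, alpha 0.05 (taken as two-sided) and 80% power.

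n per arm = 2 x (1.960 + 0.842)^2 x (10.55 / 4.15)^2 = 2 x 7.849 x 6.463 = 101.5, so 102. Allowing for 20% dropout: 102 / 0.8 = 127.5, so 128 per arm and 256 in total. This agrees with the article. The planned standardised effect is 4.15 / 10.55 = 0.39 SD. No figure is stated for the domain analyses.

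**2. Regression to the mean in question 3, with zero treatment effect.** Expected improvement among choosers = (1 - rho) x baseline gap, where rho is the correlation between T0 and T2. Both inputs are assumed.

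| Gap | rho | Apparent improvement |
|---|---|---|
| 1 SD | 0.6 | 0.4 SD |
| 1 SD | 0.7 | 0.3 SD |
| 1 SD | 0.8 | 0.2 SD |

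**3. How large could the gap be?** Under normality, if one third choose a domain and choice follows severity perfectly, they average about 1.09 SD worse than the mean. If half choose it, the maximum is about 0.80 SD. A gap of 1 SD is therefore near the upper limit for a commonly chosen domain.

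**4. Simulation over wider ranges.** Zero effect; rho 0.5 to 0.8; correlation between choice and severity 0.3 to 1.0; share choosing the domain 0.2 to 0.5 (all assumed).

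| Contrast | Range | Middle case (rho 0.7, correlation 0.6, share 0.33) |
|---|---|---|
| Improvement among choosers, intervention arm | 0.05 to 0.70 SD | 0.20 SD |
| Choosers minus non-choosers, intervention arm | 0.10 to 0.88 SD | 0.30 SD |
| Intervention minus control, subgroup defined identically in both arms | within 0.004 SD of zero | 0.00 SD |

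The middle case agrees with the formula: 0.3 x 0.6 x 1.09 = 0.20 SD.

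**5. Which grouping variables are protected by randomisation?**

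- T0 questionnaire scores: both arms, before randomisation (2.7, Table 1). Protected.
- Decision-aid and intake priorities: formed in both arms, but after allocation is disclosed (2.7). The decision-aid research data described are usage logs (2.6.2.3), and coach records are described for the intervention group (2.6.2.1). Not protected, and possibly not available for controls.
- Domain worked on during the intervention: formed during treatment and changeable. Not protected.

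**6. Price of the randomised contrast.** Power = Phi(4.15 / (10.55 x sqrt(2/n)) - 1.96), with assumed subgroup sizes and before any gain from T0 adjustment.

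| Completers per arm | Power for 4.15 points | Difference detectable with 80% power |
|---|---|---|
| 20 | 24% | 9.4 points (0.89 SD) |
| 34 | 37% | 7.2 points (0.68 SD) |
| 51 | 51% | 5.9 points (0.55 SD) |

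An interaction test has less power than these.

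**The case against.** The best defence is that the article calls these analyses exploratory and words the hypothesis cautiously. No efficacy claim depends on them, and the randomised comparison of every domain outcome is already planned in 2.15.1.2. The article also condenses a fuller protocol, to which the model and adjustment for an exploratory analysis are commonly left. Restriction to the intervention arm is implied by the wording and not stated.

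Most of this stands, and it limits the severity. It does not remove the point. The grouping variable is stated in the article, and an exploratory label weakens the claim without removing the bias.

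A reader might go further in four ways that the documents do not support.

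- **That controls' domain priorities already supply a randomised comparison, since they too complete the decision aid and intake.** Those priorities are formed once the participant can know the allocation, and nothing says that they are kept as research data for controls.
- **That the analysis is bound to confirm the hypothesis.** The size depends on how closely choice follows baseline severity. Section 2.5 says that values and preferences also enter, and the low end of the simulated range is 0.05 SD.
- **That the 0.2 to 0.4 SD applies to all three questions, or matches the planned 0.39 SD.** It concerns question 3 only. It is a within-group change on a domain scale, whereas 0.39 SD is a between-group difference on the PDQ-39.
- **That early dropouts necessarily count fewer domains.** Several domains can be prioritised at the intake itself.

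**Conclusion.** The point holds in a limited form. The domain groups are self-selected after randomisation and can change with progress. Question 3 is in effect an uncontrolled before-after comparison in which regression to the mean can pass for domain-specific benefit: 0.2 to 0.4 SD if choosers start 1 SD worse and rho is 0.8 to 0.6, and less where choice follows severity less closely. Gap, correlation and share choosing are all assumptions. For questions 1 and 2 confounding by need and engagement is expected, but the documents give no basis for its size. The primary result and the planned arm comparisons of secondary outcomes are unaffected. Severity is minor.

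**What to change.** 1. Define domain need from the T0 questionnaires in Table 1: ISI and ESS for sleep, HADS for stress, LAPAQ for exercise, DHD15-index for nutrition, PAM and GSES for self-management.
2. For each domain, estimate intervention versus control on the matching T2 outcome, adjusted for its T0 value, with an arm-by-T0-score interaction.
3. For multiple versus single, use the number of domains with poor T0 scores, with cut-points fixed before analysis, and compare arms across that number.
4. Keep comparisons by chosen domain within the intervention arm if they are of interest, but report them as descriptive and not as evidence of a domain-specific effect.
5. Do not rest the randomised comparison on decision-aid or intake priorities.

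**Cost.** Analysis wording only; no new data are needed. The Trial status section reports 219 randomised and none finished at 20 November 2025, so on that status the change can precede the outcome analysis. The question shifts somewhat, from benefit in those who targeted a domain to benefit in those who needed it. Power is low (about 24% to 51% for 4.15 points with an assumed 20 to 51 completers per arm, and less for interactions), so the results should be given as estimates with intervals.

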#### Methods in analysis to handle protocol non-adherence and any statistical methods to handle missing data

2.15.3

Statistical analysis will be performed based on the intention-to-treat principle. Missing data will be handled using maximum likelihood estimation within the linear mixed-effects models, under the assumption that data are missing at random (MAR).

#### Plans to give access to the full protocol, participant level-data and statistical code

2.15.4

The data gathered in this project will be made available upon reasonable request to the international research community via the Radboud Data Repository (RDR). All resulting publications will be published Open Access (gold open access). The statistical code will be published with restricted access and will be available upon reasonable request.

### Oversight and monitoring

2.16

#### Monitoring

2.16.1

Due to the nature of this study, it has been classified as not subject to the Dutch Medical Research Involving Human Subjects Act (WMO) by the local accredited Medical Research Ethics Committee (MREC). As such, the study is not required to follow the standard procedures involving an independent monitor. Nevertheless, as the coordinating center, the study team remains accountable to the sponsor and is required to adhere to all applicable laws and guidelines governing the quality of scientific research, as would be expected for WMO compliant studies. Yearly status updates on the study will be presented to the study sponsor, the funding body and the involved consortium of this study. This study is a low-risk study and therefore, a Data Safety Monitoring Board is not indicated.

#### Adverse event reporting and harms

2.16.2

All adverse events (AEs) reported by the participants or observed by the lifestyle coach or study staff will be documented. The investigator will report all SAEs to the sponsor (Radboudumc) without undue delay after obtaining knowledge of the events by means of a SAE-form. An overview of all SAEs is provided in the annual summary report.

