#### Step 3: remote coaching by lifestyle coach

2.5.3

When the participant needs more guidance than the online tools can provide, the next step includes remote personal coaching by the lifestyle coach (coaching mode). This differs from the continuous guidance provided throughout the stepped care model (guidance mode) in the frequency and content of the sessions. In the guidance mode, the lifestyle coach monitors the progress throughout and evaluates whether other approaches are needed. The progress is evaluated by discussing interim goals with participants. These evaluations are documented by the coach for clinical purposes and not included as research data. In the coaching mode, active coaching is provided to support the participant in changing behavior within a specific lifestyle domain. The number of sessions will be decided upon in mutual agreement with the participant, but this will be more frequent than in the guidance mode. Although the focus shifts to one-on-one guidance, the digital tools from step 2 can still be used to support the lifestyle change. Lifestyle coaching is, at this point, not part of the formal care pathways for people with PD. Lifestyle coaches in this study are trained to reach a sufficient level of PD-specific expertise, analogous to the way we train other allied health professionals as part of the Dutch national ParkinsonNet approach (40, 41). Examples of PD specific issues that may interfere with adherence to lifestyle advice include frontal executive problems, difficulties with dual tasking, fatigue and complex changes in the effectiveness of symptomatic pharmacotherapy. An essential part of the training of lifestyle coaches is to clarify which other professionals within ParkinsonNet can offer further detailed guidance, if the lifestyle coach feels insufficiently equipped to address a particular issue himself or herself (see step 4). Furthermore, they are trained to recognize PD related red flags (such as unintended weight loss or balance problems) requiring referral to healthcare professionals (step 4).

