##### Cost-effectiveness

2.6.2.1

We will perform a cost-effectiveness analysis from a societal perspective. Data on the frequency and duration of healthcare service utilization will be collected through a questionnaire at T1 and T2. The healthcare services include, but are not limited to, the use of allied healthcare, hospital, social care services (e.g., physiotherapists, neurologist, social workers). The questionnaire allows participants to report additional healthcare disciplines that are not listed. In addition, the use of assistive devices purchased during the study period will be recorded, including whether these were reimbursed through insurance. Additionally, to expand the cost-effectiveness analysis beyond healthcare utilization, participants receive questions regarding their work and productivity status at all time points (T0, T1, T2). In this context, productivity refers to both labor force participation and on-the-job performance (68, 69). For each participant in the intervention group, the lifestyle coach will record the amount of guidance provided, the use of digital tools, and the extent of lifestyle coaching. These elements will be included in the economic evaluation. Specialized care (step 4) is evaluated using a questionnaire on healthcare utilization at T1 and T2. The QoL related outcomes resulting from the EQ-5D-5L questionnaire enables the derivation of utility scores and the estimation of quality-adjusted life years (QALYs), which will be incorporated into the cost-effectiveness analysis.

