There are also a few potential challenges we anticipate. First, there is a risk of limited external validity. Individuals already interested in lifestyle interventions are more likely to enroll, while those less interested may be harder to reach. Analysis of participants in previous studies at our center indicates that the sex distribution aligns with the Dutch PD population, but older adults and non-native Dutch individuals are underrepresented (80). We aim to include people across all age categories and socio-economic backgrounds. This is particularly challenging since the approach is mainly based on eHealth, and offered in Dutch. To address this, we capitalize on our rich experience around diversity when including participants (81–83). We will implement proactive strategies such as targeted outreach to underserved populations and selective advertising. Additional measures include offering technical support and providing paper-based alternatives for the assessments when necessary. Moreover, due to the personalized nature of the intervention, it can be tailored to the individual participant’s needs and abilities. Second, there is a risk of selection bias. Since the control group will not receive any intervention after the intake at the start of the study, we anticipate an increased dropout risk in this group. We aim to prevent this by keeping them involved with the study by sending them biannual newsletters and invitations to the yearly symposium for people with PD organized by our center. Also, we decided to give these participants access to the information in the lifestyle decision aid, to promote compliance (84). Furthermore, we kept the burden of assessments low by performing them fully remote, restricted to questionnaires and a wrist monitor that will be sent to people’s homes. Third, there is a potential risk of contamination between the intervention and the control group. Blinding of the participants is difficult in an intervention study using a non-pharmacological intervention. We will try to get as close to blinding as possible by minimizing information about the intervention for the control group, and by naming the groups the guided and independent lifestyle interventions. We expect the impact of possible contamination to be minimal, because it is difficult to keep up with a behavioral change on the long term without (structural) guidance (85). At the end of the study, participants will be asked to indicate which group they believe they were allocated to, in order to assess the impact. Also, the control group only has access to the publicly available tools and therefore not to all tools used in the intervention group. Importantly, our present approach will reveal how the proposed intervention performs, over and above current clinical situation, including the ability of people with PD to access the available interventions themselves.

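### After intake only the intervention arm has scheduled coach contact, and the coach is a named route for detecting adverse events, so AE and SAE counts by arm are open to ascertainment bias

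*Protocol article*

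**What the plan says.** Section 2.16.2 of the protocol article (Adverse event reporting and harms) gives the capture rule: "All adverse events (AEs) reported by the participants or observed by the lifestyle coach or study staff will be documented". It names three routes: the participant, the lifestyle coach and study staff. For serious events it adds: "The investigator will report all SAEs to the sponsor (Radboudumc) without undue delay after obtaining knowledge of the events". An overview of SAEs goes into an annual summary report.

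Contact with the coach differs by arm:

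- **Intervention arm.** Section 2.5 (stepped care text under Figure 3) sets the monitoring frequency "within a range of once every month to once every 3 months". Section 2.5.3 says that sessions in coaching mode are more frequent than this. It also says of the coaches that "they are trained to recognize PD related red flags (such as unintended weight loss or balance problems) requiring referral to healthcare professionals".
- **Control arm.** Section 2.7 states: "The control group receives no further coaching after the intake". The Discussion makes the same point: "Since the control group will not receive any intervention after the intake at the start of the study".

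Two sources reach both arms on the same schedule. Section 2.7 says: "All participants will receive a set of questionnaires at T1 and T2". Section 2.6.2.1 says: "Data on the frequency and duration of healthcare service utilization will be collected through a questionnaire at T1 and T2", and its list of services includes hospital care. Table 1, which lists the primary and secondary outcome measures, contains no item on adverse events, falls or injuries.

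**The concern.** An event enters the record only if someone learns of it. One of the three named observers is present after intake in one arm only, and that observer is trained to notice problems such as weight loss and impaired balance. These are plausible harms of an intervention that includes exercise and nutrition. An equal number of true events could therefore yield more recorded events in the intervention arm.

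Two things are at stake. First, any table of adverse events by arm would be hard to read, because a difference could reflect harm, detection or both. Secondly, serious events are passed on only once the investigator knows of them, so the annual SAE overview inherits the same imbalance and may under-record control-arm events. The Discussion also expects more dropout among controls, which would reduce their contact further.

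**Working it through.** The article gives no figure for adverse event rates or capture, so there is none to reproduce. The check sets out the contact schedule and then shows how unequal capture carries through to the counts.

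**1. Scheduled coach contacts in the 12 months after intake**

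- Intervention, longest interval: 12 months / 3 months = 4.
- Intervention, shortest interval: 12 months / 1 month = 12, with more in coaching mode.
- Control: 0 (section 2.7).

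**2. Other contacts after intake, as described in the article**

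- Questionnaires sent by e-mail at 6 and 12 months: both arms.
- Newsletters twice a year and an invitation to the yearly symposium: both arms.
- A second week with the wrist monitor at 12 months, for about two-thirds of participants: not restricted by arm.
- A helpdesk for questions about the monitor or the decision aid, and process-evaluation interviews: not restricted by arm.

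These give participants and staff some opportunity to report or notice events in either arm. None is described as including an enquiry about adverse events.

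**3. Effect of unequal capture when the true risk is equal**

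Let p be the true risk in both arms, and c_I and c_C the probabilities that an event is recorded in the intervention and control arms. The recorded risks are p·c_I and p·c_C, so

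apparent risk ratio = (p·c_I) / (p·c_C) = c_I / c_C.

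The true risk cancels. All values of p, c_I and c_C below are assumptions; none stands in the article.

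| c_I | c_C | Apparent risk ratio | Recorded risks if p = 20% |
|---|---|---|---|
| 0.9 | 0.9 | 1.00 | 18% vs 18% |
| 0.9 | 0.7 | 0.9/0.7 = 1.29 | 18% vs 14% |
| 0.9 | 0.5 | 0.9/0.5 = 1.80 | 18% vs 10% |
| 0.8 | 0.4 | 0.8/0.4 = 2.00 | 16% vs 8% |

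**4. How often a naive test would find a difference that does not exist**

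This uses a two-sided 5% test of two proportions with 128 per arm (section 2.8) and no dropout.

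| Capture (c_I vs c_C) | p = 10% | p = 20% | p = 30% | p = 40% |
|---|---|---|---|---|
| 0.9 vs 0.7 | 8.5% | 13.8% | 20.1% | 27.8% |
| 0.9 vs 0.5 | 23.9% | 45.4% | 65.6% | 81.7% |
| 0.9 vs 0.9 | 5% | 5% | 5% | 5% |

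The article plans no such test. The table only shows what would happen if the counts were compared as collected.

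**The case against.** The strongest reply is that the article promises no comparison of harms. None of its four objectives concerns safety, section 2.15 contains no adverse event analysis, and section 2.16.2 commits only to documenting events and reporting serious ones. The study is described as low-risk. This stands, and it limits the severity: no planned analysis is invalidated. It does not remove the point, because documenting all adverse events in a randomized trial invites a table by arm, and the SAE overview depends on the same capture.

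A second reply is that the article is condensed. How events are elicited may be set out in protocol version 2.2, which is not shown. This also stands, and the fix is conditional on it. A reader might infer that events are captured only spontaneously, but the text does not say whether participants' reports are solicited. Nor does Table 1 settle the matter, since it lists outcome measures and is not a full case report form. What does not depend on the unseen document is the combination of two stated facts: the coach is a detection route, and coaching after intake is confined to one arm.

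A third reply is that study staff are a route open to both arms, and that the healthcare-use questionnaire captures hospital care in both. A reader might go further than the point made here and conclude that harms cannot be compared between arms at all. The article does not support that, because the questionnaire is a symmetric source, although a partial one: a fall or injury that leads to no care would not appear in it.

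Finally, a reader might take a risk ratio of 2 as an estimate of the bias. It is only the ratio of two assumed capture probabilities, and other plausible pairs give about 1.3 or 1.8.

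**Conclusion.** The point holds in a limited form. As described, the rule in section 2.16.2 lets adverse event capture depend on arm, with about 4 to 12 or more scheduled coach contacts a year against none after intake. AE and SAE counts by arm are not comparable without a risk of ascertainment bias. The likely direction is against the intervention, with control-arm events under-recorded.

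The size cannot be derived from the article. Under assumed capture probabilities and equal true risks, the apparent risk ratio runs from about 1.3 to 2.0. This rests on two assumptions: that coach contact raises the chance of an event being recorded, and that the full protocol contains no identical enquiry in both arms. The primary endpoint and its analysis are untouched. The change is worth making because it is cheap, but it is not a threat to the trial's main conclusion.

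**What to change.** First check whether the full protocol already puts the same adverse event question to both arms. If it does, one sentence in section 2.16.2 saying so is enough. If not:

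1. Add the same short safety item to the T1 and T2 questionnaires in both arms, covering for example falls, injury, hospital admission and other events since the last questionnaire. For participants already past T1, let the T2 item cover the full 12 months.
2. Base any between-arm description of harms on those items plus hospital use from the healthcare-use questionnaire, and give the number of respondents in each arm, because more control dropout is expected.
3. List events detected by coaches or staff separately by source, without comparing them by arm.

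This was still feasible at the reported status: on 20 November 2025, 219 participants had been randomized and none had finished. The first participant was included on 25 November 2024, so the earliest T2 assessments fall due at about that time, and the item should be added promptly. It should start on the same date in both arms; the 1:1 blocked randomization should keep those who miss it roughly balanced.

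The cost is a few questions and one sentence on reporting. The drawbacks are slight extra burden, recall over 6 to 12 months, and a recall period that differs between participants according to whether they had already passed T1.
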